# STUDY SYNOPSIS

## TITLE

Pharmacokinetic study of single oral administration of yokukansan (YKS: TJ-54) in healthy volunteers

## STUDY OBJECTIVE

To evaluate the pharmacokinetics and safety of Tsumura Yokukansan Extract Granules for prescription (hereinafter referred to as “TJ-54”)after single oral doses of 7.5g （1 sachet 2.5g x 3 sachets）, 5.0g （1 sachet 2.5g x 2 sachets）, and 2.5g （1 sachet 2.5g x 1 sachet） in healthy volunteers

## ENDPOINTS

Pharmacokinetics and safety assessment

## STUDY POPULATION

### Subjects

Healthy volunteers

### Target Sample Size to Complete Study

At least 15 subjects

### Inclusion Criteria

1) Age 20-44 years, inclusive (at the time of informed consent)

2) Subject body mass index (BMI) is between 18.5 and 25 kg/m2

3) Genders: Both

4) Willing and able to provide written, signed informed consent

### Exclusion Criteria

1) Subjects with a history of allergic reactions to drugs (including Kampo medicines) and food(s).

2) Female subjects who are pregnant, breastfeeding or planning to become pregnant.

3) Subjects who have participated in another clinical trial within the past 16 weeks.

4) Subjects who have had their blood drawn or donated > 400mL of blood within 12 weeks of study drug administration.

5) History of significant hepatic, cardiovascular or hematological disease.

6) Subjects with hepatic steatosis.

7) Subjects who can’t stop taking of alcohol and/or tobacco products within 3 days of study medication dosing.

8) Use of any medications (e.g., antipsychotic, antifungal, antihypertensive, Kampo medicine, etc.) within 7 days prior to study drug administration.

9) Use of supplements containing atractylodes lancea rhizome, poria sclerotium, cnidium rhizome, uncaria hook, Japanese angelica root, bupleurum root, and/or glycyrrhiza within 3 days of study medication dosing.

10) Use of any agent within 7 days prior to study drug administration.

11) Subjects with abnormal clinical laboratory values inappropriate for the study in the opinion of the principal investigator/subinvestigator.

12) Subjects who are deemed ineligible for other reasons by the principal investigator/subinvestigator.

13) Subjects of HCV antibody, HBs antigen, and/or HIV antibody positive.

## STUDY DESIGN

Randomized crossover study

## DOSAGE AND ADMINISTRATION

Single oral administration of TJ-54 of 7.5g (1 sachet 2.5g x 3 sachets), 5.0g (1 sachet 2.5g x 2 sachets), and 2.5g (1 sachet 2.5g x 1 sachet).

## SCHEDULE OF TIME AND EVENTS

Subjects will be randomly assigned to Groups A – C after enrollment, and three different dosages will be administered to the same subject at three separate times. The three dosage periods will be designated as phase I, phase II and phase III with a washout period of greater than 4 weeks between each treatment period, i.e., between phases I and II, and phases II and III (Table 1).

Table 1 Dosing Schedule

|  | Phase I | Washout period | Phase II | Washout period | Phase III |
| --- | --- | --- | --- | --- | --- |
| Gp A | 7.5g | > 4 weeks | 2.5g | > 4 weeks | 5.0g |
| Gp B | 2.5g | > 4 weeks | 5.0g | > 4 weeks | 7.5g |
| Gp C | 5.0g | > 4 weeks | 7.5g | > 4 weeks | 2.5g |

## OTHER FACTORS FOR CONTROL

1) Supplements containingg atractylodes lancea rhizome, poria sclerotium, cnidium rhizome, uncaria hook, Japanese angelica root, bupleurum root, and/or glycyrrhiza are strictly prohibited from 3 days prior to dispensing the study medication until completion of each treatment phase. In addition, foods and drinks containing caffeine, alcohol, carbonated water, glycyrrhiza (that there is a notation in ingredients), garlic and citrus fruits (grapefruit, orange, tangerine, etc.) are prohibited from 3 days prior to dispensing the study medication until completion of each treatment phase. Meals must be consumed before 20:00 on the eve of study drug administration, and subjects must have fasted from 20:00 until the postdose, 4-hour sampling is complete. However, water may be consumed at any time.

2) Smoking is prohibited within 7 days prior to dosing study medication until the completion of each treatment phase of the study.

3) Use of other medications is prohibited within 7 days prior to dosing study medication until the completion of each treatment phase of the study.

## STUDY PERIOD

May 2012 – December 2012

# BACKGROUND

Yokukansan, a classical herbal prescription, is composed of seven crude drugs, namely, atractylodes lancea rhizome, poria sclerotium, cnidium rhizome, uncaria hook, Japanese angelica root, bupleurum root, and glycyrrhiza. TJ-54 is yokukansan manufactured as convenient granules via Tsumura`s proprietary dry granulation method and officially approved as Kampo extract formulation for prescription under the provisions stipulated in “Report No. 120 of the Central Pharmaceutical Affairs Council, Ministry of Health and Welfare dated May 31, 1985”. TJ-54 has broad clinical applications for the treatment of insomnia1), peevishness in children, and behavioral and psychological symptoms of dementia2)-5). Reported pharmacological effects of TJ-54 ameliorated aggressiveness6)-9). Recently, several basic studies have clarified that the serotonergic nervous9)-11) and glutamatergic12)-15) systems are associated with the mechanisms of TJ-54.

While reports on the pharmacological effects of TJ-54 abound, pharmacokinetic studies of TJ-54 are difficult to execute due to complexity of multiple constituents. Although pharmacokinetic parameters of single isolated constituents are occasionally seen in literatures, pharmacokinetic investigation of TJ-54 as a compound prescription in animal and human studies is insubstantial16).

The “Preliminary absorption study of yokukansan (YKS:TJ-54)in healthy volunteers TJ-54 (TJ-54-4-2)” was conducted from April 2011 to identify constituents that were absorbed after a single oral dose of 7.5g of TJ-54 in healthy adults17). From the results of the previous preliminary absorption study, 3 compounds of pharmacological actions have been suggested in TJ-54 (geissoschizine methyl ether11), 18)-20), hirsuteine20), and 18β-glycyrrhetinic acid13)) were confirmed in plasma.

The reports of licorice is one of the configuration crude drugs TJ-54, the long-term high intake are likely to develop pseudoaldosteronism, there is suggested 18β-glycyrrhetinic acid and glycyrrhetinic acid 3-O-glucuronide are causal compounds21). Therefore, this study also confirms the plasma concentration of glycyrrhetinic acid 3-O-glucuronide. This finding is believed to provide important data for the side effect studies.

The objective of this study is to evaluate the pharmacokinetics and safety of TJ-54 by measuring the plasma concentration of four TJ-54 derivative compounds.

The present study will be conducted in accordance with the trial protocol and standards specified under the MHLW ordinance regarding Good Clinical Practice (GCP), MHLW ordinance regarding Good Post-Marketing Surveillance/Study Practice (GPSP), and Article 14, Paragraph 3, and Article 80, Paragraph 2 of the Pharmaceutical Affairs Law.

# STUDY OBJECTIVE

## Study Objective

To evaluate the pharmacokinetics and safety of Tsumura Yokukansan Extract Granules for prescription (hereinafter referred to as “TJ-54”)after single oral doses of 7.5g (1 sachet 2.5g x 3 sachets), 5.0g (1 sachet 2.5g x 2 sachets), and 2.5g (1 sachet 2.5g x 1 sachet) in healthy volunteers.

## TYPE OF STUDY

Post-marketing clinical trial

# STUDY POPULATION

## Subjects

Healthy adult volunteers

## Target Sample Size

At least 15 completed subjects

[Rationale for Sample Size Determination]

15 subjects have been determined according to the conventional sample size required to evaluate pharmacokinetics. For a definition of the term “completed”, refer to 5.3.1.

## Inclusion Criteria

1) Japanese

2) Age 20-44 years, inclusive (at the time of informed consent)

3) Subject body mass index (BMI) is between 18.5 and 25 kg/m2

4) Genders: Both

5) Subject is willing and able to provide written informed consent

[Rationale for Inclusion Criteria]

This study is directed to Japanese. The purpose of setting the lower age limit is to select adults with the ability to make an informed decision about study participation, while the upper age limit serves to dampen physiological effects of aging from older subjects. Body mass index (BMI) within normal range as specified by the Japan Society for the Study of Obesity (JASSO) is included to minimize the effects of obesity on the distribution of the study medication.

## Exclusion Criteria

1) Subjects with a history of allergic reactions to drugs (including Kampo medicines) and food(s).

2) Female subjects who are pregnant, breastfeeding or planning to become pregnant.

3) Subjects who have participated in another clinical trial within the past 16 weeks.

4) Subjects who have had their blood drawn or donated > 400mL of blood within 12 weeks of study drug administration.

5) History of significant hepatic, cardiovascular or hematological disease.

6) Subjects with hepatic steatosis.

7) Subjects who can’t stop taking of alcohol and/or tobacco products within 3 days of study medication dosing.

8) Use of any medications (e.g., antipsychotic, antifungal, antihypertensive, Kampo medicine, etc.) within 7 days prior to study drug administration.

9) Use of supplements containing atractylodes lancea rhizome, poria sclerotium, cnidium rhizome, uncaria hook, Japanese angelica root, bupleurum root, and/or glycyrrhiza within 3 days of study medication dosing.

10) Use of any agent within 7 days prior to study drug administration.

11) Subjects with abnormal clinical laboratory values inappropriate for the study in the opinion of the principal investigator/subinvestigator.

12) Subjects who are deemed ineligible for other reasons by the principal investigator/subinvestigator.

13) Subjects of HCV antibody, HBs antigen, and/or HIV antibody positive.

[Rationale for Exclusion Criteria]

1)-5) ensure the safety of subjects, 6)-12) eliminate subjects who may interfere with the objectives of the study, and 13) ensure the safety of analysts.

# STUDY METHOD

## STUDY DESIGN

This is a randomized crossover study. Study medication will be administered to the same subjects after a washout period of greater than 4 weeks.

## DOSAGE AND ADMINISTRATION

Subjects will be randomly assigned to Groups A – C after enrollment, and three different dosages will be administered to the same subject at three separate times. The three dosage periods will be designated as phase I, phase II and phase III with a washout period of greater than 4 weeks between each treatment period, i.e., between phases I and II, and phases II and III (Table 1).

Table 1 Dosing Schedule

|  | Phase I | Washout period | Phase II | Washout period | Phase III |
| --- | --- | --- | --- | --- | --- |
| Gp A | 7.5g | > 4 weeks | 2.5g | > 4 weeks | 5.0g |
| Gp B | 2.5g | > 4 weeks | 5.0g | > 4 weeks | 7.5g |
| Gp C | 5.0g | > 4 weeks | 7.5g | > 4 weeks | 2.5g |

## STUDY COMPLETION; SUBJECT DISCONTINUATION, WITHDRAWAL OR REPLACEMENT

### Study Completion

Each treatment period will be considered complete after the 48-hour blood sampling and testing at the end of the period.

The study will conclude after the completion of the 3 treatment phases.

### Subject Discontinuation or Withdrawal

The investigator may terminate or withdraw a subject from the study if the subject meets any of the following criteria:

1) Requests withdrawal or declines to participate;

2) Experiences an adverse events (AE) that undermines the continuation of the study in the opinion of the principal investigator;

3) Unable to take the study medication;

4) Judged as ineligible to continue the study by the principal investigator.

### Discontinuation Procedure

The principal investigator/subinvestigator must document subjects who discontinue the study and the reason(s) for it, measures taken and follow-up in the Case Record Form (CRF). If discontinuation is for safety reasons, appropriate measures must be taken and subjects should be followed to resolution and receive follow-up evaluations until their safety is assured, except in cases where consent cannot be obtained from the subjects.

### MANAGEMENT OF SUBJECTS

All subjects are under close supervision of the principal investigator/subinvestigator during their participation in the clinical trial.

The principal investigator/subinvestigator will instruct all subjects to comply with the following directions.

1) Supplements containingg atractylodes lancea rhizome, poria sclerotium, cnidium rhizome, uncaria hook, Japanese angelica root, bupleurum root, and/or glycyrrhiza are strictly prohibited from 3 days prior to dispensing the study medication until completion of each treatment phase. In addition, foods and drinks containing caffeine, alcohol, carbonated water, glycyrrhiza (that there is a notation in ingredients), garlic and citrus fruits (grapefruit, orange, tangerine, etc.) are prohibited from 3 days prior to dispensing the study medication until completion of each treatment phase. Meals must be consumed before 20:00 on the eve of study drug administration, and subjects must have fasted from 20:00 until the postdose, 4-hour sampling is complete. However, water may be consumed at any time.

2) Smoking is prohibited within 7 days prior to dosing study medication until the completion of each treatment phase of the study.

3) Use of other medications is prohibited within 7 days prior to dosing study medication until the completion of each treatment phase of the study.

# CLINICAL TRIAL MATERIAL (CTM)

## PROPRIETARY NAME AND MANUFACTURER

Study medication: Tsumura Yokukansan Extract Granule (for prescription)

Code number: TJ-54

Manufacturer: Tsumura & Co.

## CONSTITUENTS, DOSAGE FORM, STORAGE

Ingredients/Content: 7.5g of TJ-54 contains 3.25g of dried extract of the following ratio of crude drugs.

JP Atractylodes Lancea Rhizome ...... 4.0g

JP Poria Sclerotium ............................ 4.0g

JP Cnidium Rhizome .......................... 3.0g

JP Uncaria Hook …............................ 3.0g

JP Japanese Angelica Root ................. 3.0g

JP Bupleurum Root ............................ 2.0g

JP Glycyrrhiza .................................... 1.5g

(JP: The Japanese Pharmacopoeia)

Excipients: JP Magnesium stearate, JP Lactose Hydrate

Dosage form: Extract granule

Packaging: One heat-sealed sachet contains 2.5g of extract granule

Storage: Store in cool, dry place. Avoid contact with moisture and direct sunlight.

## DOSAGE AND ADMINISTRATION

Single oral administration of TJ-54 of 7.5g (1 sachet 2.5g x 3 sachets), 5.0g(1 sachet 2.5g x 2 sachets), and 2.5g(1 sachet 2.5g x 1 sachet).

## SUPPLY AND DELIVERY

The clinical trial material (CTM) will be supplied and delivered by the sponsor to the institution for free after the study contract is signed between the two parties.

## STORAGE AND HANDLING

The study drug administrator will store and handle the CTM in appropriate manner.

## RETRIEVAL

The sponsor will retrieve all unused CTM after inspection by the sponsor.

# MEASUREMENTS AND EVALUATIONS

## INSPECTION AND OBSERVATION ITEMS

### Screening Items

The principal investigator/subinvestigator will conduct the following medical interview, clinical observations and laboratory tests within 7 days prior to the start of the trial, and select prospective subjects based on their results. Tolerance screening date is ±1 day.

Demographics: date of birth (DOB), gender, race, present illness, current medications, drug and food allergies, past medical history, alcohol intake, smoking history

Clinical findings: subjective symptoms, objective findings, edema

Physical examination: height, weight, BMI, body temperature (axillary), blood pressure (seated), pulse (seated)

Laboratory tests:

1) Hematology

Erythrocytes, leukocytes, platelets, hemoglobin, hematocrit

2) Blood chemistry

Total protein, blood urea nitrogen (BUN), creatinine, uric acid, aspartate transaminase (AST), alanine aminotransferase (ALT), total bilirubin (T-Bil), alakaline phosphatase (ALP), gamma-glutamyl transpeptidase (γ-GTP), albumin (Alb), prothrombin time (PT), total cholesterol (TC), C-reactive protein (CRP), HbA1C, kalium (K)

3) Urinalysis

Urinary glucose

Urinary Pregnancy test (females only)

Viral tests: HCV antibody, HBs antigen, HIV antibody

### Predose Tests

The principal investigator/subinvestigator will perform the following clinical observations and laboratory tests within one day prior to dispensing the study medication, and select prospective subjects based on the comprehensive analysis of test results.

Clinical findings: subjective symptoms, objective findings, edema

Physical examination: body temperature (axillary), blood pressure (seated), pulse (seated)

Laboratory tests:

1) Hematology

Erythrocytes, leukocytes, platelets, hemoglobin, hematocrit

2) Blood chemistry

Total protein, blood urea nitrogen (BUN), creatinine, uric acid, aspartate transaminase (AST), alanine aminotransferase (ALT), total bilirubin (T-Bil), alakaline phosphatase (ALP), gamma-glutamyl transpeptidase (γ-GTP), albumin (Alb), prothrombin time (PT), total cholesterol (TC), C-reactive protein (CRP), HbA1C, kalium (K)

Urinary Pregnancy test (females only): Phase I only, inspection at the time of screening.

### Test at the Administration

Clinical findings: subjective symptoms, objective findings

### Tests at the End of Study

At the end of each treatment phase, the principal investigator/subinvestigator will perform the following clinical observations and laboratory tests.

Clinical findings: subjective symptoms, objective findings, edema

Physical examination: body temperature (axillary), blood pressure (seated), pulse (seated)

Laboratory tests:

1) Hematology

Erythrocytes, leukocytes, platelets, hemoglobin, hematocrit

2) Blood chemistry

Total protein, blood urea nitrogen (BUN), uric acid, aspartate transaminase (AST), alanine aminotransferase (ALT), total bilirubin (T-Bil), alkaline phosphatase (ALP), gamma-glutamyl transpeptidase (GTP), albumin (Alb), prothrombin time (PT), total cholesterol, C-reactive protein (CRP), kalium (K)

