| Clinical exam | ○ | ○ | ○ |  |  |  |  |  |  |  |  |  |  |  |  | ○ | |
| Urinary pregnancy testNote2 | ○ | |  |  |  |  |  |  |  |  |  |  |  |  |  |  | |
| Lab tests Note3  sample volume | ○  8mL | ○  8mL |  |  |  |  |  |  |  |  |  |  |  |  |  | ○  8mL | |
| TJ-54 dosing |  |  |  | ○ |  |  |  |  |  |  |  |  |  |  |  |  | |
| MealNote4 |  | ○ |  |  |  |  |  |  |  | ○ |  | ○ |  |  | ○ | ○ | |
| PK Note3  sample volume |  |  | ○  8mL |  | ○  8mL | ○  8mL | ○  8mL | ○  8mL | ○  8mL | ○  8mL | ○  8mL | ○  8mL | ○  8mL | ○  8mL | ○  8mL | ○  8mL | |
| Safety assessment |  |  |  |  |  |  |  |  |  |  |  |  |  |  |  |  | |

Note 1: The above schedule is for Phase I. Screening tests conducted 7 days prior to dosing of study medication will not be performed in Phases II and III, i.e., predose tests one day before dosing and other tests scheduled thereafter will be performed.

Note 2: Conduct in females only. Urinary pregnancy test is performed at the time of screening tests in Phase I, the Phases II and III are carried out the day before drug dosing of study medication.

Note 3: The total blood draw will be 368mL [screening: 8mL x 1, 120mL x 3 phases {(8mL x 2 for laboratory tests, 8ml x 13 for pharmacokinetic) x 3}]. In addition, the 4, 12, 24, and 48-hour sampling will be collected before meal.

Note 4: Supplements containingg atractylodes lancea rhizome, poria sclerotium, cnidium rhizome, uncaria hook, Japanese angelica root, bupleurum root, and/or glycyrrhiza are strictly prohibited from 3 days prior to dispensing the study medication until completion of each treatment phase. In addition, foods and drinks containing caffeine, alcohol, carbonated water, glycyrrhiza (that there is a notation in ingredients), garlic and citrus fruits (grapefruit, orange, tangerine, etc.) are prohibited from 3 days prior to dispensing the study medication until completion of each treatment phase. Meals must be consumed before 20:00 on the eve of study drug administration, and subjects must have fasted from 20:00 until the postdose, 4-hour sampling is complete. However, water may be consumed at any time.

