### Safety assessment

Safety will be determined from the overall assessment of adverse events, clinical findings, physical examination, and laboratory results. As a rule, the average of screening and predose test results will become baseline values (test results obtained exclusively from screening will be used as they are) and changes observed after dosing will be taken into account.

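### Creatinine is measured at screening and before every dose but at the end of no treatment phase, so its change after dosing cannot be assessed

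*Protocol*

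**What the plan says.** The protocol sets out three blood chemistry lists.

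- **Screening (7.1.1):** "Total protein, blood urea nitrogen (BUN), creatinine, uric acid, aspartate transaminase (AST), alanine aminotransferase (ALT" and further items.
- **Predose (7.1.2):** "Total protein, blood urea nitrogen (BUN), creatinine, uric acid, aspartate transaminase (AST" and further items, taken "within one day prior to dispensing the study medication". Note 1 to Table 3 repeats these in Phases II and III, where "predose tests one day before dosing and other tests scheduled thereafter will be performed".
- **End of phase (7.1.4):** "Total protein, blood urea nitrogen (BUN), uric acid, aspartate transaminase (AST), alanine aminotransferase (ALT" and further items. This list applies to all three phases: "At the end of each treatment phase, the principal investigator/subinvestigator will perform the following clinical observations and laboratory tests". The Study Completion section places that point at 48 hours: "Each treatment period will be considered complete after the 48-hour blood sampling and testing at the end of the period".

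Section 8.2.2 draws the safety conclusion from adverse events, clinical findings, physical examination and laboratory results together. It takes the mean of the screening and predose results as baseline, as a rule, and adds that "changes observed after dosing will be taken into account".

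**The concern.** Safety is part of the stated objective, and 8.2.2 assesses it by change from baseline. An analyte with a baseline and no later value cannot contribute to that assessment. Creatinine is in this position in every phase and therefore at every dose level. No analysis plan can repair this, because the values would never have been scheduled.

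The predose tests of Phases II and III do fall after an earlier dose. They come more than 4 weeks later, however, and they serve as baseline for the next phase. They would show only a rise that persisted through the washout, and no scheduled test of any kind follows Phase III. The Background section raises pseudoaldosteronism in connection with licorice constituents, and potassium is measured at the end of each phase. A creatinine value from the same sample would help in reading a shift in potassium or BUN.

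**Working it through.** **1. Comparison of the lists**

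| Analyte | Screening (7.1.1) | Predose (7.1.2) | End of phase (7.1.4) |
| --- | --- | --- | --- |
| Creatinine | yes | yes | no |
| HbA1c | yes | yes | no |
| BUN, uric acid, potassium | yes | yes | yes |
| The other 10 (total protein, AST, ALT, bilirubin, ALP, γ-GTP, albumin, PT, cholesterol, CRP) | yes | yes | yes |
| Number of analytes | 15 | 15 | 13 |

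The difference is 15 − 13 = 2 analytes, creatinine and HbA1c. Losing HbA1c is harmless, since it would not be expected to move within 48 hours of a single dose. That reasoning does not carry over to creatinine.

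**2. Whether another section restores it**

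- Section 7.1.3 (test at administration) lists clinical findings only and no laboratory test.
- Tables 2 and 3 carry a single laboratory row without naming analytes, so the lists in 7.1.1, 7.1.2 and 7.1.4 govern.
- The protocol gives no reason for the omission.

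**3. Count of scheduled values**

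- Creatinine per subject: 1 at screening + 3 predose = 4 baseline values, and 0 at the end of a phase.
- Phases with an end-of-phase value: 0 of 3 for creatinine, 3 of 3 for BUN, uric acid and potassium.
- Over the target of at least 15 completers: 15 × 3 = 45 predose values, at the least, with no end-of-phase partner.

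**4. Blood volume, before and after the change**

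The inputs are in 7.1.5 and Note 3 to Table 3: 8 mL at screening and, in each phase, 2 laboratory draws and 13 pharmacokinetic draws of 8 mL each.

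- Stated total: 368 mL.
- Reproduced: 8 + 3 × (8 × 2 + 8 × 13) = 8 + 3 × (16 + 104) = 8 + 360 = 368 mL.
- With creatinine added: one of the two laboratory draws per phase is the 48-hour sample, so no draw is added and the total remains 368 mL. Creatinine values per subject rise from 4 to 4 + 3 = 7, and the end-of-phase panel from 13 to 14 analytes.

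**The case against.** The strongest reply is that the shorter list may be deliberate. Section 7.1.2 gives the predose panel a selection purpose, 7.1.4 does not, and two analytes are dropped together. Section 8.2.2 speaks of an overall assessment and does not promise a paired value for every analyte, and 7.1.6 names only adverse events as the safety parameter. The protocol plans no renal comparison by dose and names no nephrotoxic risk. The subjects are healthy adults aged 20 to 44 who take three single doses of a marketed product more than 4 weeks apart. BUN, uric acid, potassium, blood pressure and edema are all still checked at the end of each phase. Unscheduled creatinine testing also remains possible when an adverse event is followed up.

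Much of this stands as a limit on the weight of the point. Renal monitoring is reduced, not lost. The figure of 45 counts missing pairs and says nothing about missed events. The pharmacokinetic results and the sample size are untouched.

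It does not remove the point. A baseline-only role for creatinine is stated nowhere, and 8.2.2 makes no exception for it. Unscheduled testing depends on some other signal appearing first, so it cannot replace a scheduled value in all subjects.

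**Conclusion.** The concern holds. Creatinine has a scheduled baseline before all three doses and no scheduled value at the end of any phase. The change from baseline described in 8.2.2 therefore cannot be formed for it within a phase: 0 of 3 phases, and at least 45 unpaired predose values with 15 completers. The comparison rests on the written lists alone. It assumes that the unspecified laboratory rows in Tables 2 and 3 follow those lists and that the target number of subjects completes all three phases. The point is a modest gap in the safety data that is worth correcting: the correction is very cheap, and values not collected cannot be recovered later.

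**What to change.** Add creatinine to the blood chemistry list in 7.1.4, to be run on the 8 mL laboratory sample already planned at 48 hours in each phase. This is a one-word amendment. It needs no extra tube, visit or blood volume, and it costs one more assay per subject per phase, or 15 × 3 = 45 assays for 15 completers.

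If the omission is intended, state in 7.1.4 and 8.2.2 that creatinine (and HbA1c) are screening and baseline tests only and are excluded from the assessment of change. That costs nothing but leaves the protocol without post-dose creatinine. Either way, 7.1.2, 7.1.4 and 8.2.2 should be made to agree.
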